## Abstract

**Background:**

Antimicrobial resistance (AMR) is a growing health concern, particularly in Africa, and is predicted to become the leading cause of death after cancer by 2050. Factors like overuse or inappropriate use of antibiotics contribute to this crisis. People living with HIV (PLWH) are particularly vulnerable to AMR with potential drug-drug interactions between antiretroviral and antimicrobial agents against common organisms like
*Mycobacterium tuberculosis.* There is limited data on the concentrations of commonly used antimicrobial agents in people living with HIV in resource-limited settings. Therapeutic Drug Monitoring (TDM) offers a promising approach to optimize antibiotic dosing and improve treatment outcomes for those with sub-optimal drug concentrations. TDM has been recommended for PLWH on anti-tuberculosis treatment due to sub-optimal drug concentrations found in a significant proportion of those with TB.

**Objectives:**

The main objectives of this study are to determine the concentrations of selected antimicrobial agents in people living with HIV requiring antimicrobial therapy and to assess the utility of therapeutic drug monitoring in achieving therapeutic targets for PLWH receiving rifampicin and isoniazid for the treatment of tuberculosis.

**Methods:**

This prospective observational study will enroll adult PLWH receiving amoxicillin, azithromycin, ciprofloxacin, rifampicin, isoniazid, or ceftriaxone. Concentrations of these antibiotics will be measured locally using validated liquid chromatography mass spectrometry methods and high-performance liquid chromatography with ultraviolet detection. TDM with dose adjustment will be performed in a subset of participants on TB treatment. Pharmacokinetic parameters will be estimated using non-linear mixed effects models.

**Results:**

This study was reviewed and approved by the research and ethics committee in February 2024. Participant enrolment began in September 2024.

**Conclusions:**

We anticipate that the findings from this research will characterize pharmacokinetic and pharmacodynamics relationships to predict treatment response for optimal antimicrobial therapeutic and anti-tuberculosis dosing among people living with HIV (PLWH).

**Clinical registration:**

The study is registered with Pan African Clinical Trials Registry, registration number PACTR202409710100607, registration date 07 August 2024,
pactr.samrc.ac.za/TrialDisplay.aspx?TrialID=31764

## Introduction

Antimicrobial resistance (AMR) is on the rise and is predicted to become the leading cause of after cancer by 2050, with Africa bearing a significant proportion of this burden
^
1
^. In 2019, an estimated 1.27 million deaths were attributed to antimicrobial-resistant infections, and most of these infections were bacterial
^
1
^.

Optimal dosing of antimicrobial agents is essential to achieve therapeutic concentration, maximize efficacy, and minimize both resistance and toxicity. Conversely, suboptimal drug levels may cause treatment failure, AMR, and mortality, while excessive exposures may increase toxicity and affect adherence
^
2
^. In sub-Saharan Africa, overlapping diseases lead to multi-morbidity with altered physiologic states, like those seen in infections or inflammation, and obesity
^
3
^. These require co-treatment with multiple regimens which may result in drug-drug interactions (DDI) that are often inadequately characterized. The SOUTH study found sub-therapeutic levels of rifampicin and isoniazid amongst TB-HIV coinfected patients, which were associated with delayed sputum conversion
^
4
^ and, as seen in other studies, TB relapse
^
5
^. Such findings have prompted trials of higher anti-TB doses to improve outcomes and prevent resistance
^
6–
8
^. Similarly, suboptimal antibiotic exposure has been associated with poor treatment outcomes
^
9
^ and development of resistance
^
10
^.

People living with HIV (PLWH) are at an increased risk of AMR across a range of pathogens and drug classes
^
11
^. Antibiotics are frequently prescribed in PLWH to manage co-morbidities like other sexually transmitted- and urinary tract infections as well as respiratory tract infection. Prescription rates of these vary widely, ranging from about 40% in Nigeria to as high as 85% on Tanzania
^
12
^. While this data was not available for Uganda, a recent general survey showed widespread antibiotic use across hospitals
^
13
^. Outcome data for common infections indicate an 80% treatment success rate for pneumonia, a major cause of mortality amongst especially children in Uganda. However, resistance to commonly used antibiotics is on the rise in Uganda, with reported rates exceeding 70% for ceftriaxone and ampicillin, and about 43% for ciprofloxacin
^
14
^. While it remains unclear to what extent suboptimal drug exposures directly contribute to these resistance patterns, previous studies have reported inadequate antibiotic concentrations to drive development of AMR
^
10
^. Other drivers of AMR include genetic mechanisms which also play a significant role in the emergence and spread of resistance to antimicrobials
^
15
^.

Despite the potential contribution of inadequate drug exposure to AMR, the pharmacokinetic (PK) profiles of commonly prescribed antibiotics in PLWH are not well characterized. Ceftriaxone and amoxicillin may not exhibit significant DDI with ART but some ARVs like ritonavir-boosted protease inhibitors can inhibit transporters like p-glycoprotein and multi-drug resistance protein 2, potentially increasing azithromycin exposure and raising the risk of arrythmias
^
16
^. However, no clinical PK studies have been conducted to investigate these potential interactions, and dose adjustments are not currently recommended.

Therapeutic drug monitoring (TDM) uses plasma drug concentrations to assess whether a given dose achieves optimal drug exposure
^
17
^. It helps evaluate attainment of PK targets for the antibiotics and provides objective data to guide dosing decisions. These PK targets are often based on drug exposure parameters like the area under the concentration-time curve (AUC) or peak/trough concentrations relative to the minimum inhibitory concentration (MIC) of the pathogen. For example, azithromycin and ciprofloxacin require AUC/MIC ratios of ≥5
^
18
^ and ≥125
^
19
^, respectively, while ceftriaxone has a minimum threshold of 8 mg/L
^20^. Amoxicillin efficacy depends on maintaining concentrations above the MIC for at least 40% of the dosing interval
^
21
^. However, MIC testing is rarely done in resource-limited settings due to cost constraints. For important ant-TB drugs like isoniazid and rifampicin, peak plasma concentration of 3 to 6 mg/L and > 8 mg/L are desired, respectively
^
17
^.

In resource-limited settings, where antibiotic options are often scarce, optimizing existing treatments is essential to maintain accessibility and prevent AMR. While strategies like regimen intensification, individualized drug combinations, and precision dosing can help prevent AMR, there is limited understanding of which model will be most effective for widespread implementation in low- and middle-income countries (LMICs). TDM has been successfully used for aminoglycosides and anti-TB drugs in special populations, such as PLWH and those with diabetes
^
17
^. However, there is limited data on its role in optimizing antibiotic therapy for PLWH in LMICs.

## Protocol

### Study objectives

1. To determine the concentrations of selected antimicrobial agents in people living with HIV requiring antimicrobial therapy.2. To assess the utility of therapeutic drug monitoring in achieving therapeutic targets for people living with HIV receiving rifampicin and isoniazid for treatment of tuberculosis.3. To develop and validate a population pharmacokinetic-pharmacodynamic model for use during therapeutic drug monitoring for selected antibiotics used among PLWH

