## Study design

### Participants on antimicrobial drugs

This will be a prospective observational study that will include adult patients with suspected or confirmed bacterial infection receiving amoxicillin (+/- clavulanic acid), azithromycin, ciprofloxacin. The decision to start antibiotics will be left to the managing clinician (based on clinical symptoms, full blood count, urinalysis, depending on the suspected focus) and enrolment will take place when antibiotics are initiated. We will enroll 50 participants on each of the oral antimicrobials (amoxicillin, azithromycin, ciprofloxacin). Patients being initiated on antimicrobial agents will be randomly selected, screened, and enrolled. Prescription of antibiotics will be determined by the managing clinician according to standard clinic guidelines. Participants will be requested to take the antibiotic therapy at the same time daily. At baseline, data will be collected on age, sex, gastrointestinal disorders (e.g., diarrhea and vomiting), weight, height, alcohol use, illicit drug use, and details of concomitant medications, including antiretroviral regimens. A blood sample will be drawn for measurement of serum creatinine at baseline.
Table 1 demonstrates all study procedures.

**Table 1. T1:** Study procedures.

Protocol Activity	Screen and enrolment	Day 2 +/-3days	End antibiotic Treatment	Week 2	Week 4	Week 6	Week 8
Informed Consent	x						
Clinical evaluation	x	x	x	x	x	x	X

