**Laboratory**							
Serum creatinine	x						
ALT, total Bilirubin****				x **			
PK blood draw*		x		x **	x **		
Sputum cultures		x		x **	x **	x **	x **

** for participants on TB treatment where applicable

**
*Participant follow-up*
**

Study visits will be conducted at enrolment, on day 2 for measurement of drug concentrations and the last day of antibiotic use to determine treatment outcome (after 5 – 7 days).

**
*Sparse pharmacokinetic sampling for antimicrobial drugs*
**

Sampling for measurement of antibiotic concentrations will be performed on day 2 of antimicrobial therapy. Directly observed therapy will be performed on the day of the blood draw. For those on oral azithromycin and ciprofloxacin, a pre-dose sample (trough concentrations) will be drawn, while for those on amoxicillin, a pre-dose and 6-hour blood draw will be taken. (
Table 2)

**Table 2. T2:** TDM for antimicrobials.

Drug	Administration	Time of blood draw
Amoxycillin (+/- clavulanic acid)	Oral	Pre-dose, 6 hours post dose
Azithromycin	Oral	Pre-dose (trough),
Ciprofloxacin	Oral	Pre-dose (trough),

**
*Intense pharmacokinetic sampling for antimicrobial drugs*
**

Intensive pharmacokinetic sampling will be conducted after at least 2 days of oral antibiotic use, for 20 randomly selected participants on each of these oral drugs; amoxicillin, ciprofloxacin, and azithromycin. At least 20 participants were chosen based on the target of having less than 20% relative standard error in the estimated coefficient of variation. For amoxicillin, blood will be drawn pre-dose, 0.5 h, 1 h, 1.5 h, 2h, 2.5 h, 3 h, 4h, 6h, and 8 h post-dose. For azithromycin and ciprofloxacin, blood will be pre-dose, and at 1 h, 2 h, 3h, 4h, 5h, 6h, 8h, 12h, and 24h post-dose dosing.

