### Statistical analysis

**
*Analysis of data on antimicrobial drugs: sparse pharmacokinetic data*
**

Sparse pharmacokinetic data for antimicrobials will be analysed as medians with standard deviations. We assess for the effect of covariates like age, sex, body-mass index, CD4 cell counts on drug concentrations

**
*Analysis of data on antimicrobial drugs: intensive pharmacokinetic data*
**

Non-linear mixed-effects models will be used to calculate the pharmacokinetic parameters of the drugs and this will include the maximum plasma concentration (Cmax), time to maximum plasma concentration (Tmax), and area under the plasma concentration-time curve (AUC). We will also explore the effects of covariates like age, sex, concomitant medications, and body-mass index on the pharmacokinetic parameters.

**
*Pharmacodynamic parameters*
**

We will use pharmacokinetic and pharmacodynamic models to assess the effect of the pharmacokinetic parameters on clinical response. For sparse pharmacokinetic data, we will use drug concentrations as a covariate in the linear regression models predicting clinical response. Clinical response will be defined as either clinical cure (resolution of symptoms) or clinical failure (lack of improvement in signs and symptoms of infection or recurrence of signs/symptoms of infection after initial improvement or death considered at least possibly due to the infection.

**
*Analysis of data on anti-tuberculosis drugs*
**

For participants on anti-tuberculosis drugs, we will evaluate whether dose adjustment leads to the achievement of therapeutic targets.

As an exploratory objective, using Kaplan Meier survival analysis, time to sputum culture negativity will be compared for those who received dose adjustment and those who did not receive dose adjustment within this study. We will also utilize the SOUTH dataset where drug concentrations of rifampicin and isoniazid were measured (without dose adjustment), where 78% and 84% of participants had rifampicin and isoniazid concentrations below the therapeutic targets respectively.

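### Objective 3 promises a validated PK-PD model, but the analysis section, read by its headings, leaves about 30 sparsely sampled participants per oral drug out of the population model and splits the exposure-response evidence in two

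*Protocol article*

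**What the plan says.** Under Study objectives, the third objective is "To develop and validate a population pharmacokinetic-pharmacodynamic model for use during therapeutic drug monitoring for selected antibiotics used among PLWH".

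Under Participants on antimicrobial drugs, the article states: "We will enroll 50 participants on each of the oral antimicrobials (amoxicillin, azithromycin, ciprofloxacin". Intensive sampling is planned "for 20 randomly selected participants on each of these oral drugs; amoxicillin, ciprofloxacin, and azithromycin", with ten time points each. The reason given for that size is: "At least 20 participants were chosen based on the target of having less than 20% relative standard error in the estimated coefficient of variation".

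The sparse schedule is much thinner. "For those on oral azithromycin and ciprofloxacin, a pre-dose sample (trough concentrations) will be drawn", and amoxicillin has a pre-dose and a 6-hour sample (Table 2).

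The Statistical analysis section handles the two kinds of data under separate headings:

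- **Sparse data:** "Sparse pharmacokinetic data for antimicrobials will be analysed as medians with standard deviations", plus an assessment of covariate effects on concentrations.
- **Intensive data:** non-linear mixed-effects models to obtain Cmax, Tmax and AUC, with covariates.
- **Pharmacodynamics:** PK and PD models relate PK parameters to clinical response. For sparse data, the measured concentration instead enters a regression predicting clinical response.

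**The concern.** A population model is the usual way to combine rich and sparse sampling, so that participants with one or two samples still contribute. The section headings point the other way: the model belongs to the 20 intensively sampled participants, and the other participants' samples are summarised or used raw.

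Two things follow if the section is carried out as its headings read. First, more than half of the participants per oral drug do not inform the model that Objective 3 offers for use in therapeutic drug monitoring. Second, exposure-response is estimated twice: once per unit of a model-derived parameter such as AUC, and once per unit of a single measured concentration. The two coefficients are on different scales and cannot be pooled into one estimate. The PD half of a model meant to guide dosing would then rest on very few clinical failures, although more are available at no cost.

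**Working it through.** **1. The plan's own figure for the intensive subset.** With n = 20, the relative standard error of an estimated SD is 1/√(2(n−1)) = 1/√38 = 16.2%. For an estimated CV it is √(1/(2n) + CV²/n). At the 30% CV given under Sample size this is √(0.025 + 0.0045) = 17.2%. Both are below the stated 20%, so the figure is reproduced. It is a criterion of PK precision and does not address exposure-response. The sample size of 40, raised to 50, per antibiotic is justified by a 30% effect on exposure and does not address it either.

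**2. Participants outside the intensive subset.** Taking the 20 as drawn from the 50 enrolled per oral drug: 50 − 20 = 30. At 15% attrition (the upper figure under Sample size): 30 × 0.85 = 25.5, about 25.

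**3. Information on exposure-response.** The failure rate p is an assumption, shown over 10–40%. Expected failures are n·p. For a logistic slope per SD of exposure, near no effect, SE(log OR) ≈ 1/√(n·p·(1−p)). The 95% interval is the estimate multiplied and divided by exp(1.96·SE).

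| n | p | Failures | SE | Factor each way |
|---|---|---|---|---|
| 20 | 0.10 | 2 | 1/√1.8 = 0.745 | 4.3 |
| 20 | 0.20 | 4 | 1/√3.2 = 0.559 | 3.0 |
| 20 | 0.40 | 8 | 1/√4.8 = 0.456 | 2.4 |
| 50 | 0.10 | 5 | 1/√4.5 = 0.471 | 2.5 |
| 50 | 0.20 | 10 | 1/√8 = 0.354 | 2.0 |
| 50 | 0.40 | 20 | 1/√12 = 0.289 | 1.8 |

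The rows for 50 are a best case. Exposure predicted from one or two samples is less certain than exposure from ten, and 15% attrition would reduce both groups (20 × 0.85 = 17; 50 × 0.85 = 42.5).

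**4. Cross-check by comparing failures with cures.** At p = 0.20, the exposure difference detectable with 80% power (two-sided 5%, normal approximation) is (1.96 + 0.84)·√(1/f + 1/(n−f)) SD, where f is the number of failures. For 4 versus 16 this is 2.80 × 0.559 = 1.57 SD. For 10 versus 40 it is 2.80 × 0.354 = 0.99 SD. Using everyone helps materially, but the analysis remains imprecise.

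**The case against.** The strongest replies, and what stands of each:

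- **A reader might infer that modelling is confined to the 20.** The article never says so. The restriction is read from the headings of the Statistical analysis section, and the Abstract mentions mixed-effects modelling without limit. This stands: the point is about how the section reads. The Abstract does not name the data to be modelled, however, while the analysis section gives the sparse data another use.
- **A reader might infer that the PD analysis has about four failures per drug.** That takes 20% from a background sentence in the Introduction, "Outcome data for common infections indicate an 80% treatment success rate for pneumonia". The sentence concerns pneumonia, with emphasis on children, whereas participants here are adults with HIV and any suspected or confirmed bacterial infection. The objection stands, so only a range is used above.
- **A reader might infer that the design cannot support the word validated, or that no data are available for it.** Bootstrap, predictive checks and cross-validation need no held-out participants, and an article may leave such methods to a full protocol or analysis plan. This stands: silence on the validation method is not the finding.
- **The sparse data are not unused.** They enter a covariate analysis and a regression on response. This is correct. The issue is that, as the section reads, they stay outside the population model.
- **A test on the sparse-only participants would be limited.** One trough for azithromycin and ciprofloxacin cannot test Cmax or Tmax, and the participants come from the same study. This stands and limits the fix.
- **Scope.** Objective 3 may also cover ceftriaxone and the TB drugs. The earlier SOUTH dataset is mentioned only in the anti-TB analysis. The point is therefore confined to the three oral drugs, which have both sampling schemes.

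**Conclusion.** The concern holds in a limited form. Objective 3 and the Statistical analysis section do not match. As its headings read, the section builds the population model on 20 participants per oral drug, leaves about 30 (about 25 after attrition) outside it, and divides the exposure-response evidence between two analyses that cannot be combined. Over an assumed failure rate of 10–40%, bringing in all 50 would narrow the interval for an odds ratio per SD of exposure from a factor of about 4.3–2.4 each way to about 2.5–1.8 at best. Even then the PD part is exploratory.

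This rests on reading scope from headings, on the 20 being a subset of the 50, on the assumed failure range, and on a large-sample approximation that is rough at 2 to 8 events. The measured trough concentrations and the observed response proportions are not affected. The documents do not show that the model will go unvalidated, or that validation is impossible.

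**What to change.** 1. State in the Statistical analysis section that intensive and sparse samples of each oral drug are modelled together.
2. State that clinical response is related to model-based exposure in all participants of that drug, and label this exploratory.
3. Before pooling, the model built on the intensive subset can be checked by predicting the concentrations of the sparse-only participants, reporting bias and precision. For azithromycin and ciprofloxacin this tests trough prediction only; for amoxicillin it tests trough and 6-hour concentrations. It should be called a split-sample check, not external validation. Internal evaluation of the final pooled model is acceptable.
4. Reword Objective 3 as a developed and internally evaluated population PK model with exploratory exposure-response analysis.

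The cost is some modelling work and a more modest PD claim. No additional participants, visits or samples are needed.

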### Study outcomes

**
*On antibiotics*
**

**Primary endpoints**

Pharmacokinetic parameters

Trough concentrations (Ctrough) for amoxicillin, ciprofloxacin, azithromycin and ceftriaxone

Pharmacodynamic parameters

Clinical response to antibiotics through the time of treatment will be assessed. Clinical response is either clinical cure (resolution of symptoms) or clinical failure (lack of improvement in signs and symptoms of infection OR recurrence of signs/symptoms of infection after initial improvement.

**
*On TB treatment*
**

Pharmacokinetic parameters

Maximum concentrations (Cmax) and area under the concentration-time curve (AUC) defined as the total exposure for rifampicin, isoniazid

Pharmacodynamic parameters

1. Clinical response will be assessed according to the World Health Organization definitions of cure, completed and treatment failure, which will be extracted from the clinic database.2. Occurrence of adverse drug reactions

## Methods

### Study site

The study will be conducted at the Infectious Diseases Institute (IDI) which is an out-patient clinic in Kampala, Uganda, where around 8000 PLWH are currently being provided with care, of whom 250 are initiated on TB treatment annually. Participants who are on intravenous medication will be enrolled at Mulago National Referral Hospital which handles both medical and surgical in-patients.

### Study participants

Participants will be included if they fulfil the following criteria:

**
*Inclusion criteria*
**

1. A personally signed and dated informed consent document2. An adult of 18 years and above living with HIV3. Patients being initiated on or currently receiving antibiotics which may include: amoxicillin (+/- clavulanic acid), azithromycin, ciprofloxacin, rifampicin, isoniazid, ceftriaxone4. Participants who are willing and able to comply with scheduled visits, treatment plan, laboratory tests, and other study procedures.

**
*Exclusion criteria*
**

1. Patients who discontinue antibiotics for any reason following initiation2. Patients receiving antibiotics only for prophylaxis

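### In the oral-antibiotic cohorts, exclusion criterion 1 can only remove people after enrolment, so failures that lead to stopping would be lost from the primary clinical-response endpoint

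*Protocol article*

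**What the plan says.** All references are to the Protocol article.

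- **Study participants, exclusion criterion 1:** "Patients who discontinue antibiotics for any reason following initiation". The inclusion list names the drugs covered: "amoxicillin (+/- clavulanic acid), azithromycin, ciprofloxacin, rifampicin, isoniazid, ceftriaxone". It admits patients starting one of these drugs and patients already taking one.
- **Participants on antimicrobial drugs** (the three oral agents, 50 participants each): "enrolment will take place when antibiotics are initiated".
- **Primary endpoints:** "Clinical response is either clinical cure (resolution of symptoms) or clinical failure", with failure given as "clinical failure (lack of improvement in signs and symptoms of infection OR recurrence of signs/symptoms of infection after initial improvement". The Statistical analysis section adds "death considered at least possibly due to the infection" to failure.
- **Participant follow-up:** one of the visits is on "the last day of antibiotic use to determine treatment outcome", after 5–7 days.
- **Safety assessment:** participants who become pregnant stay in the study and only their PK data are censored. TB participants undergoing dose adjustment have every adverse event reported and followed until it resolves or stabilizes.

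**The concern.** An eligibility criterion should be decidable before a person enters the study. In the oral cohorts this one is not, because enrolment and the start of treatment coincide and stopping comes later. Applied as worded, it drops enrolled people because of something that happened to them on treatment.

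That event is not neutral. A patient who is not improving is a natural candidate for a stop or a switch, and lack of improvement is what the response endpoint counts as failure. The rule therefore selects on something close to the outcome. At stake is the clinical-response result in the three oral cohorts, which would describe only those who stayed on the drug. An analysis plan could not repair this later if follow-up of the removed participants was never collected.

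**Working it through.** **1. Can the criterion act at screening?** In the oral cohorts, enrolment is at initiation and the criterion concerns events after initiation. Every qualifying event therefore follows enrolment. No text in the article confines the rule to PK data or keeps stoppers in the response analysis. The pregnancy rule in Safety assessment shows the alternative: the participant stays and only the PK data are censored.

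**2. The plan's own figure.** Sample size starts from 40 per antibiotic and allows 10–15% attrition for withdrawal and loss to follow-up.
- 40/(1 − 0.10) = 44.4, rounded up to 45.
- 40/(1 − 0.15) = 47.1, rounded up to 48.
- The stated 50 is slightly more generous and tolerates 1 − 40/50 = 20% loss.

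The allowance does not name removal for stopping. It also concerns precision for drug exposure. Spare numbers do not correct a selected response rate.

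**3. Effect on the observed failure rate.** Let p be the true cure rate, f the share of failures who stop and g the share of cured patients who stop. After removal:

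observed failure = (1 − p)(1 − f) / [(1 − p)(1 − f) + p(1 − g)]

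Inputs:
- n = 50 per oral drug, from the article.
- p = 80%, assumed. It is borrowed from the Introduction ("Outcome data for common infections indicate an 80% treatment success rate for pneumonia"), where it is background and not a design value. It gives 10 failures and 40 cures.
- f and g are assumed throughout, as the article gives neither.

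| f | g | Failures left | Cures left | Observed failure | Observed cure |
|---|---|---|---|---|---|
| 0 | 0 | 10 | 40 | 10/50 = 20.0% | 80.0% |
| 25% | 0 | 7.5 | 40 | 7.5/47.5 = 15.8% | 84.2% |
| 50% | 0 | 5 | 40 | 5/45 = 11.1% | 88.9% |
| 75% | 0 | 2.5 | 40 | 2.5/42.5 = 5.9% | 94.1% |
| 50% | 10% | 5 | 36 | 5/41 = 12.2% | 87.8% |
| 25% | 25% | 7.5 | 30 | 7.5/37.5 = 20.0% | 80.0% |
| 0 | 10% | 10 | 36 | 10/46 = 21.7% | 78.3% |

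The cure rate is overstated when f exceeds g, unchanged when they are equal, and understated when g exceeds f.

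**4. TB participants.** Rifampicin and isoniazid are on the inclusion list of antibiotics, so criterion 1 covers them. Read literally, it excludes a participant who stops after a reaction. For participants on an adjusted dose, Safety assessment requires that same reaction to be reported and followed. The two sections pull in opposite directions, and the article does not say which prevails.

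**The case against.** Much can be said on the other side, and part of it stands.

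- **The criterion may be meant for screening.** Patients already on treatment are admitted, and ceftriaxone patients are sampled after at least one dose. For them the rule can sensibly mean that someone already off the drug is not enrolled. This stands for those patients. It does not rescue the oral cohorts, which enrol at initiation, and the wording does not express that intent.
- **Safety data.** A reader might infer that dose-adjusted TB participants who stop for toxicity vanish from the safety results. The documents do not support this. Their adverse events must all be reported and followed, and the Data Monitoring Board reviews toxicities in this group. TB response is taken from the clinic database, so it does not depend on study visits. The other antibiotics have no planned adverse-reaction endpoint to lose.
- **All failures and deaths lost.** This too might be inferred, and it is too strong. A participant who completes the course without improving is still assessed at the end and counted as a failure. The analysis section counts infection-related death as failure, and nothing says that death is treated as discontinuation.
- **Exposure–response.** A reader might infer that this analysis is biased as well. If stopping depends on the outcome alone, an exposure odds ratio is unchanged. Bias on that scale requires stopping to depend also on exposure, given the outcome, and the article gives no evidence of this.
- **Size.** The 80% is a pneumonia background figure and the stopping shares have no source. That is correct, so the table only illustrates.
- **Infection ruled out.** Patients may enrol with suspected infection and stop because there is none. They have no meaningful cure or failure, so simply counting everyone would also be wrong. The fix allows for this.
- **Analysis sets belong elsewhere.** An article may leave them to the full plan, but here it states an eligibility rule, and that stated rule is what needs changing.

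**Conclusion.** The point holds for clinical response in the three oral cohorts. As worded, criterion 1 is a post-enrolment removal tied to a primary endpoint, and failures that lead to stopping would be lost. The direction is upward for cure if failures stop more often than cured patients, which is plausible but not shown. Under the stated assumptions (20% true failure, no cured patient stopping, 25–75% of failures stopping), observed failure falls to between 15.8% and 5.9%. The true size cannot be derived from the article.

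For dose-adjusted TB participants the finding is narrower: Study participants and Safety assessment contradict each other and must be reconciled.

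**What to change.** - Delete exclusion criterion 1, or reword it to cover only patients already off the drug before enrolment.
- Keep enrolled participants who stop in the clinical-response analysis and the TB adverse-reaction analysis, and record the reason for stopping.
- Classify a stop or switch for lack of improvement under the existing clinical-failure definition.
- Report separately those stopped because infection was ruled out.
- Restrict only the PK analysis set, to participants with at least one valid concentration, keeping samples taken before the stop.
- State that adverse-event reporting for dose-adjusted TB participants continues after a stop, so that Study participants and Safety assessment agree.

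The cost is an amendment to one criterion, a few lines on analysis sets, a recorded reason for stopping and an outcome assessment for those who stop. No extra participants are needed. The downside is that the reported cure rate may be less favourable.
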